Various strategies for reducing the proportion of NMICs have been tested and evaluated: 1) obtaining a second opinion on the indication for a caesarean before proceeding [20]; 2) encouraging normal, midwife-assisted deliveries outside the hospital [21, 22]; 3) establishing guidelines based on recommendations of professional associations [23, 24]; and 4) auditing indications for caesareans and providing feedback to health professionals, combined with instituting best practices for managing labour and performing caesareans [25]. A meta-analysis of 10 randomized controlled trials in high-income countries showed a 19 % reduction in caesarean rates using one or a combination of the different approaches cited above. The most effective strategies were clinical audits with feedback (RR = 0.87; 95 % CI = 0.81, 0.93), continuous quality improvement strategies (RR = 0.74; 95 % CI = 0.70, 0.77), and multi-faceted interventions combining several approaches (RR = 0.73; 95 % CI = 0.68, 0.79) [26, 27].

Furthermore, the use of SMS (Short Message Service) technology appears to have a positive, and less costly, impact on the continuing education of healthcare providers in sub-Saharan Africa [28–30]. Indeed, studies on its use have shown SMS is easy to implement and produces positive results in terms of improved knowledge and practices among health professionals in different contexts [31–33].

While the results of randomized controlled trials in high-income countries are encouraging [25], we found no evidence that these interventions, whether alone or in combination, are effective in reducing NMIC rates in low- or middle-income countries.

The objective of the DECIDE (Appropriate decision for caesarean section in Burkina Faso) trial is to evaluate the effectiveness and understand the implementation of an intervention combining three potentially effective approaches for reducing NMIC rates: 1) training in best practices during labour and delivery to favor vaginal delivery for low-risk women; 2) clinical audits based on objective criteria for the main indications for caesareans; and 3) SMS-based reminders to support decisions regarding clinically indicated caesareans.

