In addition to the diagnostic reasoning criteria for caesarean indications, the expert committee also developed good-practice criteria to assess whether the caesarean was performed at the proper time and appropriately. Those criteria are presented in Table 2.

**Table 2 Tab2:** Caesarean quality criteria

ᅟ	ᅟ
− Patient must be given clear information on the indication for the caesarean. − Elapsed time between decision and incision must be no longer than 30 min. − Preference is given to using local or regional anaesthesia. − Patient receives prophylactic antibiotics. − Misgav Ladach surgical technique is used. − Joel-Cohen skin incision is used. − Delivery is done using controlled cord traction rather than manually. − In post-operative care, patients without complications resume liquid diet after 6 h. − In post-operative care, high-risk patients (morbid obesity, pre-eclampsia, history of thromboembolism) undergo thromboembolism prevention therapy.	In each hospital, all caesareans performed over the same given period will be evaluated. One point will be attributed for each criterion met (0 for those not met). For each case, total points attributed will be divided by the total number of criteria, giving a score of between 0 and 100 %. Each hospital’s quality score will be the average of the scores for all the caesareans evaluated for that hospital.

*Resource availability score*
Resource availability indicators will be measured in each hospital before and after the intervention through a systematic and standardized inventory of available resources. For each facility, a hospital environment complexity index will be calculated to reflect the availability of the different categories of resources needed to provide good-quality obstetric care [72, 73]: basic services; screening tests; basic emergency obstetric resources; intrapartum care; general medicine services; anaesthesiology; human resources; teaching and clinical resources; and clinical care protocols.

*Perinatal mortality in infants delivered by caesarean*

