We selected this indicator because we believe improvements to obstetric care prompted by audits should also have an impact on perinatal outcomes related to intrapartum care [65, 73]. Included in the definition are immediate neonatal deaths (within 24 h after birth) and fresh stillbirths; excluded are macerated stillbirths, deaths of premature infants (less than 37 weeks amenorrhea), and deaths of severely deformed infants. Perinatal mortality related to intrapartum care is defined as the number of immediate deaths and fresh stillbirths divided by the number of non-preterm caesarean deliveries in the same period.

*Intra-hospital maternal mortality among patients with caesareans*
This indicator was selected because we believe that, as in perinatal deaths, improvements in caesarean practice prompted by audits should also have a positive impact on maternal outcomes [73–75]. This indicator is defined as the ratio between the number of post-caesarean maternal deaths occurring in a hospital during the study period and the number of caesareans performed in that hospital over that period.

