### Data quality control

The quality of clinical data will be controlled in two steps. The first consists of quarterly visits by the study coordinator, who will verify that the data collection is exhaustive by comparing the number of eligible patients from the delivery register and the hospital’s surgical protocols register with the number of patient forms completed. An additional procedure will be carried out to check that the data entered in the forms matches the data in the source documents (medical records, delivery registers, surgical registers). The coordinator will verify the quality of the data collected in each form. The completeness rate will be estimated as the proportion of forms that contain 100 % of the following information: entry date, patient identity, method of admission, reason for admission, history of pregnancy, patient’s medical history, details of the obstetric examination and labour management, indication for the caesarean, technique used for the caesarean, post-operative monitoring, date of discharge, maternal and infant vital signs at discharge. The matching rate will be estimated as the proportion of forms containing information that is consistent with the source documents. When information is missing or inaccurate on any forms, the coordinator will correct those forms from the source documents in the presence of the midwife. The corrections will be made first on the paper form and then on the electronic form. Once the corrections have been made, the database will be updated. A second check for missing or abnormal data will be performed at the coordination centre and the data collected will be updated again. If necessary, missing or inaccurate information will be added and/or corrected by communicating with the midwives by telephone. To ensure data quality, there will be regular contact with the midwives (equipped with mobile telephones), who will be given lists of duplicates and missing or abnormal data and will be responsible for correcting these errors.

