### Type of analysis and treatment of hospitals lost to follow-up

We believe the acceptability of the various components of the intervention, including the caesarean audits, is high [34, 35]. Nevertheless, some hospitals may decide to withdraw from the study. For these hospitals, data collection will continue until the end of the study, in accordance with the commitment made by the hospital authorities at the time of inclusion. These hospitals will therefore not be excluded from the analysis. In accordance with the intention-to-treat analysis approach, every patient will be analyzed at the hospital where she was admitted, and each hospital will be analyzed in the group to which it was randomly allocated.

There is no data monitoring committee and no stopping rules.

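### Both mortality outcomes count only caesarean deliveries, a group the intervention is meant to change, so they cannot show harm in women who no longer have a caesarean or support a general claim of better outcomes

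*Protocol article*

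**What the plan says.** Under Assessment criteria, the protocol article lists two mortality outcomes among its secondary criteria. The first is headed "Perinatal mortality in infants delivered by caesarean"; its numerator is fresh stillbirths plus deaths within 24 hours, and this is "divided by the number of non-preterm caesarean deliveries in the same period". The second is headed "Intra-hospital maternal mortality among patients with caesareans" and is "the ratio between the number of post-caesarean maternal deaths occurring in a hospital during the study period and the number of caesareans performed", both counts being taken at the same hospital.

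Inclusion and exclusion criteria admits only women with caesarean deliveries (the first 100 per hospital per period). Data collection and processing provides a form for each caesarean and for no other delivery.

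The objective in Background includes "training in best practices during labour and delivery to favor vaginal delivery for low-risk women". Hypotheses sets a target of at least halving the rate of non-medically indicated caesareans (NMIC). It adds a secondary hypothesis of improved maternal and perinatal outcomes, without limiting it to caesareans. Analysis strategy applies the cluster-adjusted model to mortality reductions.

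On oversight, the section on hospitals lost to follow-up states: "There is no data monitoring committee and no stopping rules". Potential limitations of the trial does not mention that mortality is restricted to caesareans.

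**The concern.** Whether a woman has a caesarean is decided after randomisation, and the intervention exists to alter that decision. Conditioning both mortality outcomes on it means that the arms are compared on groups that allocation itself has shaped. Two consequences follow.

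- **Unseen harm.** A death in a woman or infant for whom no caesarean followed is in neither numerator nor denominator. No other outcome covers vaginal births, so the trial has no measure of what happens to the women whose management it changes.
- **Shifted case mix.** If the avoided caesareans are lower-risk than those that remain, deaths per caesarean go up although nobody's care has worsened.

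At stake is the secondary hypothesis on outcomes. A difference in these rates, in either direction, could be read as an effect of the intervention on mortality when it is not a randomised comparison of mortality.

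**Working it through.** The article gives no mortality rate, expected number of deaths or power for these outcomes, so there is no figure of the plan to reproduce. The check has three steps.

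**1. Who is counted**

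| Event | Numerator | Denominator |
|---|---|---|
| Death after a caesarean, prompt or delayed | yes (perinatal exclusions apply) | yes |
| Death with vaginal delivery after a caesarean was avoided | no | no |
| Maternal death before surgery | no | no |

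**2. How many women leave the measured group**

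Inputs: 11 hospitals × 100 records = 1,100 baseline caesareans per arm (Inclusion and exclusion criteria); NMIC share f = 12% to 24% (Background); target of halving (Hypotheses).

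- If the share applies to all caesareans: 1,100 × 0.12 / 2 = 66, and 1,100 × 0.24 / 2 = 132.
- If NMICs arise only within the four audited indications, 76% of caesareans (Assessment criteria): 66 × 0.76 ≈ 50, and 132 × 0.76 ≈ 100.

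**3. Case-mix effect on deaths per caesarean**

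Let r be the death risk of an NMIC relative to an indicated caesarean. The article does not give r, so I take the range 0 to 1 as an assumption. Indicated caesareans and their risk are held fixed.

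- A, number of NMICs halved: ratio of new to old rate = {[(1−f) + (f/2)r] / (1−f/2)} / [(1−f) + fr].
- B, NMIC proportion halved: ratio = [1 − f/2 + (f/2)r] / [1 − f + fr].

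With r = 0 and the share applied to all caesareans:

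- A: 1/0.94 = 1.064 (12%); 1/0.88 = 1.136 (24%).
- B: 0.94/0.88 = 1.068 (12%); 0.88/0.76 = 1.158 (24%).

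With r = 0 and NMICs confined to the 76%:

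- A: 1/(1 − 0.76×0.12/2) = 1.048; 1/(1 − 0.76×0.24/2) = 1.100.
- B: the caesarean volume becomes 0.76(1−q)/(1−q/2) + 0.24, where q is the NMIC share within the four indications. That is 0.951 (q = 12%) or 0.896 (q = 24%), and the inverse gives 1.051 or 1.116.

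With r = 0.5 and all caesareans: A gives 1.030 to 1.059, B gives 1.032 to 1.068. With r = 1 every ratio is 1.

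The rise is therefore 0 to about 16%, or 0 to about 12% under the narrower share. Taking the first 100 caesareans does not remove it, because the mix within those 100 still shifts.

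**The case against.** Several points can fairly be made for the plan.

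- **The restriction is open and has a rationale.** Both outcome headings name caesarean patients, and the text presents the maternal indicator as reflecting better caesarean practice. As indicators of caesarean care they are coherent. This stands; the fault is in using them for the wider hypothesis.
- **Delayed caesareans.** A reader might infer that harm from delay is hidden too. It is not: a delayed caesarean that is still performed stays in the rate. Only cases with no caesarean drop out.
- **A rise is not inevitable.** A reader might infer that success must push the rates up by 7% to 16%. Those are upper bounds with no deaths among NMICs. Table 1 makes lower risk plausible, since several categories require no sign of foetal distress or maternal severity. But the NMIC definition also takes in undocumented cases and uncorrected heart-rate abnormality, and no mortality by indication status is given. If NMIC falls through better documentation alone, the rates need not move, and better care could offset a rise.
- **Direction and size.** The case-mix rise runs against the hypothesised benefit, so that mechanism would not create a false one. It is also small beside sampling error. At assumed mortality of 2%, 5% or 10%, with 1,100 per arm and no clustering, the 95% limits for a risk ratio lie a factor exp{1.96√[2(1−p)/(1,100p)]} = 1.8, 1.4 or 1.3 either side, and wider with the stated variance inflation of 3. The case-mix part is therefore secondary.
- **Adjustment and intention-to-treat.** Baseline adjustment may absorb some of the measured case-mix difference, and hospitals are analysed as allocated. Neither restores the women who are not in the data.

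**Conclusion.** The concern holds in a limited form. By definition, the two mortality outcomes cannot detect harm in women diverted from caesarean and cannot support a general statement about maternal and perinatal outcomes. That conclusion needs no assumption about death rates. If the target is met through fewer caesareans, it concerns roughly 50 to 132 women per 1,100 baseline caesareans in the intervention arm.

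The case-mix effect is conditional: 0 to about 16% (0 to about 12% within the four indications), assuming that NMIC halves through real avoidance, that indicated caesareans are unchanged, and that r lies between 0 and 1.

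A reader might go further and infer that the intervention causes harm, or that the lack of a monitoring committee is itself an error. The article gives no data for the first. The second is a stated choice, relevant here only because no other route to noticing such deaths is described. The primary outcome and the sample size are unaffected. The change should be made, but the trial's main conclusion does not depend on it.

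**What to change.** 1. Add intrapartum-related perinatal deaths and maternal deaths per all deliveries, as hospital-level counts for the pre- and post-intervention periods where registers allow. Under Data quality control the coordinator already makes quarterly visits "comparing the number of eligible patients from the delivery register" with completed forms, so aggregate totals could be transcribed then. Analysis strategy already uses each hospital's pre-intervention caesarean rate, which ordinarily requires total deliveries.
2. Compare these counts by arm at hospital level, with clustering accounted for.
3. Keep the caesarean-only rates as descriptive indicators of caesarean care, and state that they are not a randomised comparison of mortality.
4. If all-delivery counts cannot be obtained, restrict the secondary hypothesis and the conclusions to outcomes among caesarean deliveries, and add the restriction to Potential limitations of the trial.

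Cost: modest extra transcription. Baseline counts would be retrospective, since that period ended in November 2014. The article does not show that registers record every death needed, and the exclusions for prematurity, malformation and macerated stillbirth may not be applicable from them. Steps 3 and 4 need only changes of text.

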### Inclusion and exclusion criteria

A hospital was eligible for the trial if it had a functional operating room and had performed at least 200 caesareans in 2012. Twenty-two public hospitals were included in the trial between May and June 2014, out of a total of 24 eligible hospitals (91.6 %). Two university hospitals were excluded due to the high number of personnel in training. The 22 hospitals in the trial are representative of Burkina Faso’s current health system, spanning the full range in terms of context (urban versus rural), level of care (district and regional hospitals) and qualifications of health personnel. This process thus guaranteed a certain external validity of the results.

The intervention directly targets health professionals who provide obstetric care in the participating hospitals, while indirectly targeting the women giving birth there. The health professionals have been trained in the management of labour and delivery, with some also trained to perform caesareans. All health professionals involved in managing deliveries in their institutions were included in the study (*n* = 978). This total consisted of obstetricians and gynaecologists (*n* = 39), general practitioners (*n* = 32), physician anaesthetists (*n* = 3), nurses (*n* = 463), and midwives (*n* = 441). Maternity services personnel who were not involved in obstetric care in the labour room were excluded from the trial (*n* = 446).

The first 100 women with caesarean deliveries in the 22 hospitals during a 6-month period in the year preceding the intervention (May 2 to November 2, 2014) were included in the study. The first 100 women with caesarean deliveries in the 6 months following the end of the intervention will also be included. As the intervention will last 1 year, the pre- and post-intervention data collection periods will cover the same months of the year to avoid any seasonality bias. Women whose caesareans were performed in another hospital and who were subsequently transferred to a participating hospital will be excluded from the study.

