### Data collection and processing

A data collection system has been set up in each of the 22 participating hospitals. This system is inspired by the WHO global survey on maternal and perinatal health [73], which considers both individual clinical data and organizational data at the health facility level. Information on the first 100 caesareans performed in the 6-month pre-intervention period and the first 100 performed in the 6-month post-intervention period in each hospital will be entered by local data collectors (midwives trained for this task). These midwives fill out a standard form for each eligible caesarean, which includes information on maternal characteristics, diagnosed complications, prenatal care, management of labour, caesarean indication and procedure, post-operative monitoring, and maternal and infant vital signs at discharge (see caesarean form in Additional file 11). This information will be obtained from hospital registers and from available medical records, whose quality and archiving are regularly monitored by the study coordinator. Data will be collected daily during both the pre- and post-intervention periods. With regard to organizational data and the knowledge evaluation questionnaire, the study coordinator will compile an inventory of the resources available in all the hospitals and will administer the questionnaires to health professionals before and after the intervention period.

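### Minor: the perinatal death rate excludes cases from its numerator that stay in its denominator, and the maternal definition counts a woman who dies after transfer out as a non-death

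*Protocol article*

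**What the plan says.** All references are to the protocol article.

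**Perinatal mortality (Assessment criteria).** The numerator is set first: "Included in the definition are immediate neonatal deaths (within 24 h after birth) and fresh stillbirths". Three groups are then removed: "excluded are macerated stillbirths, deaths of premature infants (less than 37 weeks amenorrhea), and deaths of severely deformed infants". The resulting count is "divided by the number of non-preterm caesarean deliveries in the same period".

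**Maternal mortality (Assessment criteria).** The indicator is labelled intra-hospital and relates the "number of post-caesarean maternal deaths occurring in a hospital during the study period and the number of caesareans performed in that hospital".

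**Rules that bear on the maternal indicator.**
- Inclusion and exclusion criteria: "Women whose caesareans were performed in another hospital and who were subsequently transferred to a participating hospital will be excluded from the study". The same section leaves two university hospitals out of the trial.
- Data collection and processing: the form ends with "post-operative monitoring, and maternal and infant vital signs at discharge". On sources: "This information will be obtained from hospital registers and from available medical records".
- Type of analysis and treatment of hospitals lost to follow-up: "every patient will be analyzed at the hospital where she was admitted".

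Better maternal and perinatal outcomes form one of the secondary hypotheses (Hypotheses). Both mortality outcomes are to be tested with the same GEE approach as the primary outcome (Analysis strategy).

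**The concern.** A risk should be a count of events over the units that could have had the event. The perinatal rate departs from this in two ways. Term macerated stillbirths and severely deformed term infants can never count as events, yet their deliveries stay in the denominator. And the numerator counts infants while the denominator counts deliveries, so one twin delivery can supply two events. A GEE model for a binary outcome needs one unit with a yes or no attached, and the definition does not supply it.

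The maternal indicator counts a death where it happens and a caesarean where it is done. Once the exclusion at the receiving hospital is added, a death after transfer out is counted nowhere, and the woman enters the analysis as a non-death at the hospital that operated on her. These deaths would follow serious complications, and few maternal deaths can be expected in any case. Should referral of such women change in one arm, part of any difference in the indicator would reflect where women die.

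**Working it through.** The article states no mortality rate, transfer rate or power for these outcomes, so there is no figure to reproduce. The definitions are compared first. All rates after that are assumptions used only to show the scale.

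**1. Perinatal: numerator against denominator**

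| Group | Removed from numerator | Removed from denominator |
|---|---|---|
| Preterm | yes | yes |
| Macerated stillbirth at term | yes | no |
| Severely deformed infant at term | yes | no |
| Unit counted | infants | deliveries |

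One of the three exclusions is matched and two are not.

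**2. Perinatal: size**

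Let N be term caesarean deliveries, D the qualifying deaths, m the share of term infants who are macerated stillbirths or severely deformed, and t the share of twin deliveries.
- Rate as defined: D / N.
- Matched rate: D / [N(1 + t)(1 − m)].
- Ratio of defined to matched: (1 + t)(1 − m).

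Take N = 1,000 and D = 20, so the defined rate is 20.0 per 1,000.
- Exclusions alone (t = 0), m = 1% to 4%: 20/990 to 20/960 = 20.2 to 20.8 per 1,000. The defined rate is 1–4% too low.
- With t = 5% and m = 1%: 20/(1,000 × 1.05 × 0.99) = 20/1,039.5 = 19.2 per 1,000. The defined rate is about 4% too high.
- With t = 5% and m = 4%: ratio 1.05 × 0.96 = 1.008. The two errors almost cancel.

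Between arms, the factor (1 + t)(1 − m) cancels from a rate ratio if it is the same in both. If m were 1% in one arm and 4% in the other, the ratio would be off by 0.96/0.99 = 0.97, or 3%.

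**3. Maternal: following one woman**

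A woman has her caesarean at hospital A, is transferred to B and dies there.
- At A: 0 in the numerator, because the death did not occur in A; 1 in the denominator.
- At B, if B is in the trial: 0 and 0, because she is excluded there.
- If B is outside the trial (a university hospital, for example): the death is not seen.

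**4. Maternal: size**

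11 hospitals × 100 caesareans = 1,100 per arm per period. Assume a true risk of 0.5–1.0% and that 10–30% of deaths follow transfer out.
- True deaths: 1,100 × 0.005 = 5.5; 1,100 × 0.01 = 11.
- Recorded at 0.5%: 5.5 × 0.7 to 5.5 × 0.9 = 3.9 to 5.0.
- Recorded at 1.0%: 11 × 0.7 to 11 × 0.9 = 7.7 to 9.9.

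With no true effect, the apparent risk ratio is (1 − share lost, intervention)/(1 − share lost, control):
- equal shares: 1.00;
- 20% against 10%: 0.80/0.90 = 0.89;
- 30% against 10%: 0.70/0.90 = 0.78.

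For scale against chance, the SE of the log rate ratio with d deaths per arm is √(2/d), before any allowance for clustering.
- d = 5.5: SE 0.603, and exp(1.96 × 0.603) = 3.3.
- d = 11: SE 0.426, and exp(1.96 × 0.426) = 2.3.

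The 95% interval therefore spans a factor of 2.3 to 3.3 either way.

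**The case against.** The maternal indicator is openly labelled intra-hospital, and the trial works from registers and records. Stopping at the hospital door is a recognisable choice, and asking for deaths beyond it is partly asking for another outcome. This stands in good part. The label does not tell the reader, however, that a transferred woman who dies is analysed as a non-death where she was operated on.

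A reader might infer four stronger things that the documents do not support.
- **That the comparison is biased.** Equal loss in both arms leaves the ratio at 1.00. The intervention consists of training, audit and reminders about caesarean indications, labour management and surgical quality. No component is described as acting on transfer after a caesarean, and allocation is stratified by hospital type. Unequal loss is possible, but nothing in the article shows it.
- **That both definitions lose deaths after transfer.** Only the maternal one depends on place of death. The perinatal one sets a 24-hour window and no place.
- **That the intention-to-treat rule contradicts the maternal definition.** Assigning each patient to her admitting hospital settles attribution. It neither conflicts with the definition nor recovers a death elsewhere.
- **That the maternal numerator and denominator come from different women.** The exclusion at the receiving hospital keeps women operated on elsewhere out of the count, so recorded deaths are a subset of recorded caesareans. The defect is that observation ends when she leaves.

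It is also fair to say that the perinatal mismatch hardly moves a between-arm estimate, and that the chance error in the maternal comparison far exceeds the loss illustrated. Both hold, and they set the severity.

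**Conclusion.** The point holds as a minor one, confined to two secondary outcomes; the NMIC rate is unaffected.

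The perinatal defect is certain from the wording: two of three numerator exclusions are missing from the denominator, and the units differ. Its effect is a few percent of the rate (from about 4% too low to about 4% too high under the assumed m of 1–4% and t of 0–5%), largely shared by the arms.

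The maternal loss also follows from the wording, once the definition is read with the exclusion of women transferred in and with data collection that ends at discharge. Its size is unknown. The apparent risk ratios of 0.89 and 0.78 rest wholly on assumed unequal shares of deaths after transfer and show what could happen, not what is expected.

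**What to change.** **Perinatal mortality.** Define the denominator as term infants delivered by caesarean, excluding macerated stillbirths and severely deformed infants, and apply the same exclusions to the numerator. Analyse each infant as a yes or no in the GEE, clustered by hospital, which also covers the correlation between twins. The cost is a change of wording. The caesarean form (Additional file 11) is not shown, so check that it records each infant of a multiple birth and severe deformity in survivors as well as deaths. If it does not, say so.

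**Maternal mortality.** Attribute a death to the hospital that performed the caesarean whenever it is found in the registers of any participating hospital. Report transfers out by arm and period where the records show them. State plainly that deaths after transfer elsewhere are not captured. The cost is wording and a register check. Baseline collection ended in November 2014, so the check must be made in the same way for both periods; otherwise the change from baseline would partly reflect the new rule.

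Do not add telephone tracing or a composite of death or transfer out. Tracing goes beyond the collection from registers and records that hospital administrations authorised, and it would make the later period differ from the completed baseline. The composite would itself respond to referral habits.
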